### 2.3. Setting and Recruitment

Participants who meet the inclusion and exclusion criteria will be recruited from the inpatients in the Dongzhimen Hospital affiliated to Beijing University of Chinese Medicine (BUCM), China Rehabilitation Research Center, and Peking University Third Hospital. Participating institutions and the level of the institution are listed in Table 2. The study will be advertised through the Internet and posters in communities and hospitals. The inpatients and potential participants will call an investigator and be prescreened for eligibility and will learn how to participate in this clinical trial through visits or telephone calls to our hospital. During visits to the clinical research centre of Dongzhimen Hospital affiliated to BUCM, China Rehabilitation Research Center, and Peking University Third Hospital, the accessors will explain the study to the patients, who will be asked to sign an informed consent form before voluntary participation. The participants of this study will be selected from the applicants who meet all the inclusion criteria but do not meet any of the exclusion criteria. To facilitate participation in this study, the accessors will properly adjust the evaluation and treatment schedule of the enrolled participants. Therefore, the enrolled participant will be able to complete the treatment and evaluation. Every time the enrolled participant visits, the accessors will inform the participant of the next scheduled visit, and the day before the visit, the accessors will remind the enrolled participant of the schedule by telephone.

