**Methods:**

This is a multicentre, randomized, blinded, nonacupoint (NA) acupuncture controlled, multimodal neuroimaging clinical trial. A total of 48 subjects with subacute PSA will be randomly assigned to an acupoint group or an NA control group. The acupoint group will receive acupuncture with normal needling at DU20, EX-HN1, HT5, GB39, EX-HN12, EX-HN13, and CV23. The NA control group will receive acupuncture in locations not corresponding to acupuncture points as sham acupoints. Both groups will receive identical speech and language therapy thrice a week for four weeks. The primary outcome will be the change in the aphasia quotient (AQ) score measured by the Western Aphasia Battery (WAB) test during the 12th week after randomization. Participants will be blindly assessed at prerandomization (baseline) and 4 weeks, 12 weeks, and 24 weeks after randomization. The secondary outcomes include the Boston Diagnostic Aphasia Examination (BDAE) score, the Disease Prognosis Scale score for ischaemic stroke, etc. Magnetic resonance imaging (MRI) and electroencephalogram (EEG) will also be performed at 4-time intervals as secondary outcomes. All scores and image evaluations will be taken at the same point as the linguistic evaluation. The multilevel evaluation technique will be used to assess the long-term efficacy of acupuncture therapy. MRI scans and EEG will be used to assess acupuncture-related neuroplasticity changes. *Discussion*. The results from our trial will help to supply evidence for the long-term acupuncture effects for PSA over a long follow-up period. It will provide valuable information for future studies in the field of PSA treatment. The trial was registered at the Chinese Clinical Trial Registry on 16 March 2020 (ChiCTR2000030879).

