### 2.5. Interventions

Acupuncture will be performed by registered acupuncturists with over 2 years of experience who will be trained in the standardization of the acupuncture scheme. Only sterile, stainless steel, disposable acupuncture needles (size 0.25 mm × 40 mm, product no. 20182270011; ANDE Acupuncture, Guizhou ANDE Medical Equipment, China) will be used. Both acupuncture and sham acupuncture points will be located in the limbs and head. All the participants will receive 3 treatment sessions per week (alternate days) for 4 consecutive weeks, resulting in a total of 12 sessions. Each treatment will be administered for 30 minutes. The acupuncture and sham acupuncture interventions will be performed by a consensus of acupuncture experts. To ensure strict adherence to the study protocol, the experts will receive training together and use the same techniques. The details of the acupuncture treatment are described in the Standards for Reporting Interventions in Clinical Trials of Acupuncture (STRICTA [39]) checklist in Table 3.

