### 2.7. Multimodal Data Acquisition

#### 2.7.1. MRI Data Acquisition

Patients will undergo brain MRI at prerandomization (baseline) and 4 weeks, 12 weeks, and 24 weeks after randomization. MRI scans will be performed with a 3.0-T MR scanner (Siemens AG, Germany) in the Dongzhimen Hospital affiliated to BUCM. The parameters of the sequences to be employed in this study are provided by the China Association of Brain Imaging. Sagittal structural images will be acquired using a magnetization-prepared rapid gradient-echo three-dimensional (3D) T1-weighted sequence with the following parameters: repetition time (TR)/echo time (TE) = 1900/2.13 ms, flip angle = 9°, inversion time = 1100 ms, resolution = 256 × 256, voxel size: 1.0 × 1.0 × 1.0, 1-mm slice thickness without slice gap.

RS-fMRI and task-fMRI will be performed using an echo-planar imaging (EPI) sequence with the following parameters: TR/TE = 2000/30 ms, flip angle = 90°, resolution = 64 × 64, FOV = 225 × 225, bandwidth = 2520, slice thickness = 3.5 mm with 0.7 mm slice gap, 31 axial slices, and voxel size: 3.5 × 3.5 × 3.5.

Diffusion tensor imaging (DTI) will be acquired with a diffusion-weighted, single-shot, spin-echo, echo-planar imaging sequence that uses 30 directions with *b* = 0 s/mm^2^ and *b* = 1000 s/mm^2^, slice thickness: 2 mm, gap = 0 mm, slices = 65,TR: 11000 ms, TE: 94 ms, matrix: 128 × 128, FOV: 256 × 256, and phase encode direction: *A* >> P.

All scans will be qualitatively reviewed by two radiologists to screen for possible brain lesions or structural abnormalities. fMRI data will be collected during the word-picture judgement task and at rest. fMRI data will be performed with the SPM12 (https://www.fil.ion.ucl.ac.uk/spm/software/spm12/) for MATLAB. Brain activation and connectivity changes will be compared between the two groups.

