### 2.8. Outcome Measures

#### 2.8.1. Clinical Outcome Assessments

The primary outcome will be the change in the AQ score during the 12th week after randomization. For the assessment of language functioning, the WAB with the subtests spontaneous speech, auditory comprehension, repetition, and naming is included in the test battery. The WAB test will be conducted based on a previous study [40]. Secondary outcomes include four items, the details of which are listed in Table 1.

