#### 2.8.2. Neuroplasticity Assessments

In this study, neuroplasticity changes between the two groups will be measured by MRI. Before acupuncture treatment, patients will complete the fMRI scan within 3 days. They will also have a follow-up fMRI scan within 3 days after the completion of their intervention and at 8 weeks and 16 weeks after the intervention (Figure 1). Brain activity and functional connectivity will be assessed under a resting state and a word-picture judgement task. Group differences in white matter integrity will be assessed using DTI.

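### Section 2.8.2 times the follow-up fMRI from the end of the intervention, while the abstract, section 2.7.1 and Table 1 time the same scans from randomization, and no end-of-treatment date makes the two agree

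*Protocol article*

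**What the plan says.** Two timing rules for the same scans stand in the protocol article.

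- **From randomization.** Section 2.7.1: "Patients will undergo brain MRI at prerandomization (baseline) and 4 weeks, 12 weeks, and 24 weeks after randomization". The abstract (Methods) uses the same clock for all assessments: "Participants will be blindly assessed at prerandomization (baseline) and 4 weeks, 12 weeks, and 24 weeks after randomization". It adds that scores and images are taken at the same point as the linguistic evaluation. Table 1 puts MRI, EEG, ERP and the language tests together in the W4, W12 and W24 columns.
- **From the end of treatment.** Section 2.8.2 places the follow-up fMRI "within 3 days after the completion of their intervention and at 8 weeks and 16 weeks after the intervention".

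The primary outcome follows the randomization clock. Section 2.8.1: "The primary outcome will be the change in the AQ score during the 12th week after randomization".

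Two further passages bear on when treatment ends. Section 2.5 prescribes "3 treatment sessions per week (alternate days) for 4 consecutive weeks, resulting in a total of 12 sessions". Section 2.3 states that "the accessors will properly adjust the evaluation and treatment schedule of the enrolled participants", with the aim that "the enrolled participant will be able to complete the treatment and evaluation".

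**The concern.** A scan date counted from randomization is fixed for everyone on the day of allocation. A scan date counted from completion of treatment depends on something that happens afterwards, namely how long the patient stays on acupuncture and whether sessions are postponed. With both rules in the text, a site has two conflicting instructions for the same visit.

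The groups most affected are patients who stop early and patients whose course is stretched. Under section 2.8.2 their scans would fall at other times than those of the remaining patients, and at other times than their own language tests. The Discussion acknowledges some spontaneous recovery in the subacute phase, so the time of measurement matters. Section 2.9.2 compares imaging between groups and correlates fMRI data with clinical variables, and both uses assume that the measurements belong to the same time point. Section 2.9.1 promises an intention-to-treat analysis of all participants, which fits poorly with an assessment date defined by completing treatment.

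**Working it through.** **Inputs**

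- Planned treatment: 3 sessions per week × 4 weeks = 12 sessions (section 2.5), so the planned end is about week 4.
- Offsets from the end of treatment: 0 weeks (within 3 days), 8 weeks, 16 weeks (section 2.8.2).
- Stated scan times: weeks 4, 12 and 24 after randomization (abstract, section 2.7.1; Table 1: W4, W12, W24).
- Assumption: treatment starts at randomization.

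**Formula.** Let E be the week in which the intervention ends. Section 2.8.2 gives scans at E + 0, E + 8 and E + 16.

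**Can the stated schedule be reproduced?** The first scan needs E + 0 = 4, so E = 4. The second needs E + 8 = 12, so again E = 4. The third needs E + 16 = 24, so E = 8. No single E satisfies all three. The spacing shows the same thing: the last two scans are 16 − 8 = 8 weeks apart in section 2.8.2 and 24 − 12 = 12 weeks apart in section 2.7.1. The 3-day allowance is 3/7 ≈ 0.4 week and cannot close a gap of 4 weeks.

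**Scan times under section 2.8.2**

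| End of intervention (week) | Scans (weeks after randomization) | Difference from 4 / 12 / 24 |
|---|---|---|
| 2 (early stop; completion read as last session) | 2, 10, 18 | −2, −2, −6 |
| 3.7 (12th session on about day 26; 26/7) | 3.7, 11.7, 19.7 | −0.3, −0.3, −4.3 |
| 4 | 4, 12, 20 | 0, 0, −4 |
| 5 | 5, 13, 21 | +1, +1, −3 |
| 6 | 6, 14, 22 | +2, +2, −2 |
| 8 | 8, 16, 24 | +4, +4, 0 |

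Each week by which treatment is lengthened or shortened moves every scan by one week.

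**Would changing 16 to 20 weeks be enough?** The scans would then be at E, E + 8 and E + 20. For E = 4 that gives 4, 12 and 24, as stated. For E = 6 it gives 6, 14 and 26, each 2 weeks late. For E = 2 it gives 2, 10 and 22, each 2 weeks early. Correcting the figure repairs the schedule only for the patient who ends at week 4. The starting point of the clock is a separate problem.

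Section 2.8.2 refers to Figure 1, whose content is not in the text examined here. It should be checked against the same dates.

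**The case against.** Several stronger readings are tempting, and the documents do not support them.

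- **Patients who stop have no scan date.** A reader might infer this because such a patient never completes the intervention. But the abstract, section 2.7.1 and Table 1 give every randomized patient scans at weeks 4, 12 and 24, and none of these depends on the sessions received. The defect is a conflict between two rules.
- **The primary AQ is shifted.** The abstract and section 2.8.1 time the AQ at week 12 after randomization. Stopping or missing sessions does not move it, and the wording of 2.8.2 concerns fMRI only. Multiplying a scan shift by an assumed weekly gain in AQ would therefore size an effect that this mechanism does not produce. The abstract's same-point rule does not change this. It ties images to the language assessment, and that assessment has its own fixed date.
- **The 20% drop-out in section 2.6 counts the patients affected.** That figure is the allowance for patients not included in the statistics. It is not a rate of stopping acupuncture while staying in follow-up.
- **The arms are biased in a known way.** The procedures differ, since only the acupoint group has the sublingual bloodletting and the CV23 needle. But the documents say nothing about adherence by arm.
- **Section 2.3 allows unlimited rescheduling.** The sentence is a retention measure in a recruitment section. Visit windows are detail that an article may leave to the full protocol, so the absence of a stated limit is not an error in itself. Choosing appointment days can also fit within three alternate-day sessions a week.

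All of this narrows the point. What it does not remove is that 2.8.2 prints a rule that disagrees with 2.7.1, the abstract and Table 1. Condensation for a journal may explain an omission, but not two different dates for one scan.

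**Conclusion.** The point holds as a contradiction over the timing of the secondary imaging outcomes. For a patient who ends treatment at week 4, the last scan is due at week 20 under one rule and week 24 under the other, a 4-week difference. For patients who end earlier or later, section 2.8.2 moves all three scans and separates them from the randomization-timed language tests. A stop in week 2 puts the last scan about 6 weeks before week 24, and an end at week 6 puts the first two scans 2 weeks late.

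These figures assume that treatment starts at randomization and, for early stopping, that completion means the last session received. The article does not say how 2.8.2 applies to someone who does not complete. How many patients would be affected, and the size and direction of any bias, cannot be computed from the documents. No sample size figure and no primary outcome date depends on this. It should be corrected because the conflict is plain and the remedy is cheap.

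**What to change.** 1. In section 2.8.2, time all follow-up scans at weeks 4, 12 and 24 after randomization, regardless of the number of sessions received. This matches the abstract, section 2.7.1 and Table 1. Check Figure 1 for consistency.
2. In section 2.3, make clear that the schedule adjustment does not move evaluations away from those randomization-based time points.
3. Reconcile the treatment-schedule wording of section 2.3 with the fixed calendar in section 2.5. Which treatment schedule applies is for the investigators to decide.

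The cost is wording only, with no added visits and no change to the sample size. There are two small drawbacks. Evaluations can be moved less freely for patient convenience. And in a patient whose course runs past week 4, the week 4 scan would no longer be a post-treatment scan, which is the price of measuring everyone at the same time.

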### 2.4. Eligibility Criteria

#### 2.4.1. Inclusion Criteria

Participants meeting all of the following criteria will be included in this trial: (1) diagnosed as stroke through computed tomography (CT) or MRI, 1 to 6 months after stroke onset; (2) 30 to 80 years of age (After the expert discussion and the actual situation of our country, the age range has been adjusted), the native language is Chinese, and right-handed; (3) primary school and above education with no serious heart, liver, or kidney diseases; (4) clear consciousness and no cognitive impairment; (5) normal language function before the stroke onset and dominant language dysfunction with mild limb dysfunction; (6) specific aphasia syndrome diagnosed as motor aphasia by the WAB; (7) BDAE score of 2 to 4; and (8) able to cooperate for the 30-minute MRI examination.

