### 2.2. Randomization and Blinding

Eligible patients will be randomly assigned to the acupoint group or NA control group with a 1 : 1 ratio. The randomization sequence will be generated by a third-party professional statistician using a computer-generated randomization digital table using SAS V.9.4 software (SAS Institute Inc., North Carolina, USA). An independent assessor will interview the participants and carry out the screening. Random numbers and group assignments will be confirmed immediately through short message service to the practitioners who conduct acupuncture. All participants will be blinded to the types of acupuncture. An independent, blinded assessor who does not know the group assignment will conduct the outcome evaluation after the treatment. The researcher who will oversee the statistical analysis will also be blinded, with the treatment for each group remaining unknown; however, it is impossible to blind practitioners who conduct acupuncture. The practitioner will be forbidden from discussing the type of acupuncture with the participants. We will endeavour to ensure that subjects begin the trial with similar expectations of efficacy by informing them that the provided treatments are effective. In this study, participants, assessors, and statisticians will be blinded to treatment allocation. Participants will receive treatments alone at different times to avoid communication with each other. An eye patch will be applied to patients during the acupuncture treatment. To minimize the unintentional physical cues and bias in this trial, acupuncturists will be required to emulate the same procedure for the nonacupoint control group. In addition, participants will be asked to answer the following question during week 4 to test the blinding effect: “Do you think you have received real acupuncture treatment?” The participants can choose “yes” or “no” as an answer [37, 38]. The percentage of participants who answered “yes” in both groups after the final treatment will be analyzed. If the results show no significant difference in the response to this question between the two groups, they could suggest that the blinding effect is sufficient.

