### 2.9. Statistical Analysis

#### 2.9.1. Clinical Data Analysis

All statistical analyses will be performed by a statistician from the Clinical Evaluation and Analysis Centre of Dongzhimen Hospital affiliated to BUCM using Statistical Package for the Social Sciences (SPSS) V.22.0. The statistician will be blinded to the allocation of groups. The level of significance is established at *α* < 0.05 with a two-tailed test. The main objective is to compare the change in the AQ score at week 12 from baseline between the acupoint group and the NA control group. The null hypothesis is that the acupoint group will show the same change as the NA control group, while the alternative hypothesis is that the acupoint group shows a greater improvement. Categorical data will be represented by percentages, whereas continuous data will be represented by the average, standard deviation, median, minimum value, and maximum value. For comparison with the baseline, a *t*-test or nonparametric test will be used for continuous data and nonparametric tests for categorical data. For comparison of two independent samples, if the residuals are normally distributed, the analysis of covariance (ANCOVA) will be used for the primary outcome and subgroup analysis stratified by aphasia severity, *t*-tests for other continuous data, and chi-square tests for categorical data; if the residuals are non-normally distributed, a nonparametric test will be used for both the continuous and categorical data. The results of the intention-to-treat (ITT) analysis will be used to assess the validity of the study as a whole. The ITT analysis will collect data from all the participants in this trial, and for those lost to follow-up, the last observation carried forward method will be implemented.

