## 3. Discussion

PSA has proven to be difficult to treat. There is a degree of spontaneous recovery in the subacute phase, so there are few studies on the subacute phase of PSA. However, the subacute phase also requires treatment. The extant literature shows that acupuncture is probably effective for PSA [18, 45–47]. We intend to evaluate the long-term efficacy of acupuncture in maintaining speech production function. One common problem is the lack of standardization of acupoint selection, needle retention time, number of needles used, needling depth, and needle manipulation in acupuncture research.

From 2006 to now, we attempted to explore the general acupuncture scheme based on syndrome differentiation. In our PSA acupuncture treatment programme, DU20 is located in the area at the top of the head and is particularly closely related to the regulation of brain speech activity. The EX-HN1 are the acupuncture points around the DU20, both of which are used together to benefit the brain and promote speech rehabilitation. The treatment of PSA by EX-HN12 and EX-HN13 bloodletting has a theoretical basis in TCM and unique clinical efficacy. CV23 is mainly used for the treatment of speechlessness, stabbing into the skin towards the root of the tongue, and has the effect of restoring speech. The acupuncture theory of HT5 and GB39 to be used in our study is different from the traditional meaning of these points. FMRI can help us evaluate the changes of needle-related neuroplasticity, so we have conducted fMRI experiments based on this pair of effective points for aphasia. Electroacupuncture at HT5 and GB39 may modulate language and cognition function through a complex network formed by an extensive area of the brain cortex. It is beneficial to the recovery of language function [47]. In previous studies, we have demonstrated that this acupuncture protocol has shown significant improvements in auditory comprehension, reading, and dictation in patients with subacute PSA after 4 weeks of treatment. Therefore, we would like to know more about whether this treatment programme has long-term effects in these areas and observe the association with overall linguistic changes.

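### Entry spans 1 to 6 months after stroke, but time since onset is neither a named covariate nor a stratification factor, so a chance imbalance could shift the week-12 estimate

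*Protocol article*

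**What the plan says.** - **Entry window (2.4.1).** Patients are eligible "1 to 6 months after stroke onset". Section 2.4.1 narrows other sources of variation (motor aphasia only, BDAE 2 to 4), but not this one.
- **Natural recovery (3. Discussion).** "There is a degree of spontaneous recovery in the subacute phase". No rate is given, and no correlation with time since onset.
- **Randomisation (2.2).** Patients are "randomly assigned to the acupoint group or NA control group with a 1 : 1 ratio". No stratification or minimisation factor is described.
- **Primary comparison (2.9.1).** The aim is to "compare the change in the AQ score at week 12 from baseline between the acupoint group and the NA control group", at the 5% level "with a two-tailed test".
- **Model (2.9.1).** If residuals are normal, "the analysis of covariance (ANCOVA) will be used for the primary outcome and subgroup analysis stratified by aphasia severity". No covariate is named, not even baseline AQ. Severity appears only as a subgroup factor.
- **Fallback (2.9.1).** "if the residuals are non-normally distributed, a nonparametric test will be used for both the continuous and categorical data". No adjustment is described on this route.
- **Size (2.6).** 20 analysed per group and 48 recruited, with no effect size, SD or power stated.

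**The concern.** Twelve weeks of follow-up cover roughly months 1 to 4 after stroke for a patient who enters at month 1, and months 6 to 9 for one who enters at month 6. If natural recovery slows over that span, expected AQ change depends on entry time, whatever the arm.

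Baseline AQ, the covariate most readers would supply for an unlabelled ANCOVA of change, does not stand in for entry time. Two patients with the same AQ at month 1 and month 6 can have different expected further gains.

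Two things are at stake in a small trial without described stratification. The arms may differ by chance in mean time since onset, and that difference would carry into the treatment estimate. Variation in natural recovery may also stay in the error term. Section 2.6 says the trial is meant to inform the sample size of a definitive trial, so a shifted estimate would be carried forward.

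**Working it through.** **The plan's own figure.** 20 × 1.2 = 24 per group, 48 in total, which reproduces the target. Dividing instead, 20/0.8 = 25 per group, 50 in total. The two-patient gap is immaterial here. No power is stated, so there is none to reproduce.

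**Inputs.** From the article: entry 1 to 6 months, 20 analysed per arm, two-sided 5%. Assumed: uniform entry over the window; baseline AQ already in the model; partial correlation ρ between time since onset and AQ change given baseline AQ, from 0 to 0.5; an illustrative true effect of 0.8 SD. SD means the residual SD of AQ change before time since onset is added.

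**Step 1: size of a chance imbalance.**
- SD of time since onset = 5/√12 = 1.44 months.
- SE of the between-arm difference in means = 1.44 × √(2/20) = 0.46 months; 95% range ±1.96 × 0.456 = ±0.89 months.
- The difference exceeds 0.5 month in 27% of trials and 1 month in 2.8%.

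**Step 2: effect on the unadjusted estimate.** A 1.96-SE imbalance shifts it by 1.96 × ρ × √(2/20) SD:
- ρ = 0.2: 0.12 SD
- ρ = 0.3: 0.19 SD
- ρ = 0.5: 0.31 SD

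Against a true effect of 0.8 SD these are 15% (0.124/0.8) to 39% (0.310/0.8).

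**Step 3: error rates.** Simulation under no effect, 20,000 runs, 20 per arm, both models containing baseline AQ:

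| | ρ = 0.3 | ρ = 0.5 |
|---|---|---|
| Unadjusted, all trials | 4.8% | 5.2% |
| Adjusted, all trials | 5.0% | 5.1% |
| Unadjusted, imbalance above 1.5 SE (13% of trials) | 7.8% | 12.5% |
| Adjusted, imbalance above 1.5 SE | 5.3% | 4.9% |

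Overall alpha is kept either way, and the mean estimate was close to zero throughout. The harm is conditional on the imbalance that occurs.

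**Step 4: precision and power.** Adding the covariate multiplies the SE by √(1 − ρ²) × √(1 + 1/(2n − 4)). At n = 20 the second factor, the average cost of estimating one more slope, is √(1 + 1/36) = 1.014. Power is from the noncentral t, with 37 degrees of freedom unadjusted and 36 adjusted.

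| ρ | SE ratio | Power at 0.8 SD (unadjusted 69.3%) |
|---|---|---|
| 0 | 1.014 | 68.0% |
| 0.1 | 1.009 | 68.5% |
| 0.2 | 0.993 | 69.8% |
| 0.3 | 0.967 | 72.1% |
| 0.4 | 0.929 | 75.5% |
| 0.5 | 0.878 | 80.1% |

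**Sensitivity to n.** The ITT analysis with last observation carried forward could include up to 24 per arm. The imbalance SE is then 0.42 months, the 1.96-SE shift is 0.11 to 0.28 SD for ρ of 0.2 to 0.5, and power goes from 77.4% to 76.4% (ρ = 0), 78.1% (0.2), 80.2% (0.3) and 87.2% (0.5). The pattern is the same.

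**The case against.** The strongest reply is that section 2.9.1 names no covariate at all. Silence is not exclusion, and an article commonly leaves the covariate list to the full protocol or analysis plan, neither of which is shown. This stands against the stronger reading that a reader might infer, namely that the planned model leaves time since onset out. The text neither includes nor excludes it. What remains is narrower. The article gives a wide window, its own statement about recovery, no described stratification and a small sample, and the obvious default covariate does not cover the gap. It also commits itself to a nonparametric route with no adjustment described, on which a later covariate list might have no effect.

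Second, the article never says that recovery differs between month 1 and month 6, and its Introduction says that aphasia after stroke rarely recovers spontaneously. This also stands: ρ is an assumption, and below about 0.2 adjustment gains essentially nothing. A flat statement that precision is lost is therefore not supported.

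Third, the unadjusted estimate is unbiased over randomisations and type I error is kept. This is correct, so the point is not one of systematic bias. It concerns the single allocation that will be analysed.

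Fourth, section 2.6 sets no power target, so a gain at 0.8 SD repairs no stated figure. This is true; the power figures only illustrate the balance of cost and benefit.

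**Conclusion.** The point holds in this form: given the 1 to 6 month window and the article's acknowledgement of natural recovery, time since onset should be a named adjustment factor, and at present it is not named in the analysis or in the randomisation. The documents do not show that it has been rejected as a covariate, that the estimate is biased on average, or that alpha is inflated overall.

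The size depends on a correlation that the article does not give. With uniform entry and 20 per arm, a 1.96-SE imbalance (0.89 months) moves the estimate by 0.12 to 0.31 SD for ρ of 0.2 to 0.5. The balance favours adjustment: at an assumed 0.8 SD effect it costs at most about 1.3 percentage points of power (69.3% to 68.0% at ρ = 0) and gains about 3 points at ρ = 0.3 and 11 at ρ = 0.5. It also protects the result when the arms happen to differ in entry time. This is a worthwhile improvement to the plan, not a defect that invalidates the trial.

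**What to change.** In section 2.9.1, state before unblinding that the primary ANCOVA of week-12 AQ change adjusts for baseline AQ and for months since stroke onset as a continuous covariate, with no data-driven selection. State also that both covariates are kept if residuals are non-normal, for example through a rank-based or robust ANCOVA, in place of an unadjusted nonparametric test. If the full analysis plan already fixes this, it is enough to say so in 2.9.1 and to align the fallback.

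The cost is one or two sentences and one degree of freedom for time since onset. No new data are needed, since the onset date has to be established at screening. Adjustment for centre is optional and is not part of this point.
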